**Figure 1 F1:**
[figure not shown]
**Participant flow through the RCT (based on CONSORT statement)**.

### Quantitative study

#### Design

The study will be a prospective randomized controlled trial (RCT) with three arms (i) walking programme, (ii) a supervised exercise class, (iii) usual physiotherapy of up to 8 weeks duration. Outcomes will be assessed at baseline and 3, 6 and 12 months [follow-up by pre-paid postage].

#### Controlling bias

The RCT design includes key methodological features that have been recognized as important in minimizing bias in clinical trials: true randomization, concealed allocation, specification of eligibility criteria, blind outcome assessment, blind analysis and intention-to-treat analysis.

#### Setting

A sample of patients will be recruited in Dublin, Ireland through the physiotherapy departments of acute public hospitals that provide physiotherapy treatment for people with CLBP.

#### Protocol protection

The following mechanisms will be used to ensure the trial protocol is applied consistently: protocol manuals will be developed and all involved researchers and clinicians will be trained to ensure that subject screening, assessment, random allocation and treatment procedures are conducted according to the protocol; a random sample of 20% of treatment records in each group will be audited by a researcher not involved in the day to day running of the trial to check that treatment is administered as per the protocol; if any anomalies are found all treatment records will be checked. The treatment record forms will be completed by clinicians on every patient recruited to the study.

### Study population and recruitment

#### Clinics and Clinicians

The study will be conducted in several Dublin metropolitan acute general hospitals physiotherapy departments that provide rehabilitation for musculoskeletal conditions. The relevant hospitals will be contacted by telephone and email seeking expressions of interest to participate in the study. A meeting will be scheduled with each hospital's physiotherapy department manager to outline the project and distribute the outline protocol. Information meetings will be arranged with managers and treating physiotherapists to discuss the study background, aims and methodologies and to address their queries. Reception staff will be briefed on the study recruitment process, and patient appointment systems, paperwork and filing arrangements will be made. All participating physiotherapists involved in the interventions will attend training days in the School of Physiotherapy and Performance Science, University College Dublin. These days will be delivered by various members of the research team. The main focus of the training days will be to ensure that the interventions are standardized across all centres. A cognitive behavioural therapy (CBT) approach will be emphasized and performance indicators will be set for the physiotherapists to further ensure homogeneity of the active interventions.

In advance of the training days, a detailed trial manual will be distributed to the therapists. Their role in the study will be highlighted. They will also complete the PABs PT (Pain Attitudes and Beliefs of Physiotherapists) Questionnaire to establish their biopsycho-social or biomedical orientation to the management of CLBP [36].

#### Patients

All eligible patients with chronic or recurrent LBP referred to the participating hospitals physiotherapy departments by general practitioners or hospital consultants will be invited to participate in the study by the Trial Co-ordinator in order of referral until adequate subject numbers are achieved. Patients will receive the initial contact by telephone to explain the trial procedures, to clarify interest and to screen eligibility, and will then be followed up by a letter containing the patient information sheet and an invitation to attend for baseline assessment. Suitable, interested patients will attend the relevant hospital's physiotherapy department, where detailed verbal explanations of the study protocol will be provided and, written informed consent will be sought by the Trial Co-ordinator. The Trial Co-ordinator will record the number of patients invited, the number who declined, ineligible patients and reasons.

### Eligibility Assessment

#### Clinicians

Chartered Physiotherapists who are eligible for membership of the Irish Society of Chartered Physiotherapists and are employed by one of the participating hospitals are eligible to participate.

#### Patients

At the initial telephone contact and the baseline interview the Trial Co-ordinator will use a screening checklist to verify eligibility (Table 1). The Physical Activity Readiness Questionnaire (PAR-Q)[37] will be completed to determine whether medical clearance is necessary before trial participation.

**Table 1 T1:** Eligibility Criteria for the SWIFT Trial

*Inclusion criteria*	*Exclusion criteria*
Patients with chronic (≥3 months) or recurrent (≥3 episodes in previous 12 months) LBP of mechanical origin with/without radiation to the lower limb	Currently or having received treatment for CLBP within previous 3 months

Males/females between 18–65 years	Red flags indicating serious spinal pathology, e.g. cancer, cauda equina lesion

No spinal surgery within the previous 12 months	Radicular pain indicative of nerve root compression

Patients deemed suitable by their GP/hospital consultant to carry out an exercise programme	Patients diagnosed with severe spinal stenosis, spondylolisthesis, fibromyalgia

Patients willing to attend for an 8-week treatment programme of exercise classes	History of systemic/inflammatory disease, e.g. rheumatoid arthritis

Access to a telephone (for follow-up support)	Patients with any confounding conditions such as a neurological disorder or currently receiving treatment for cancer

Fluency in English (verbal and written)	Patients with acute (< 6 weeks) or subacute LBP (6–12 weeks), provided that they have experienced < 3 LBP episodes during previous 12 months

'Low' or 'moderate' levels of physical activity measured by the IPAQ (< 600 MET-minutes/week)	Unstable angina/uncontrolled cardiac dysrhythmias/severe aortic stenosis/acute systemic infection accompanied by fever

	Medico-legal issues

	Pregnancy

### Randomisation

Patients who have consented to participate will be randomly allocated in accordance with recognised procedures, by computer-generated random allocation sequences that will be prepared centrally by the trial statistician. This sequence will be used to randomly allocate each consenting, numbered subject to one of three study groups: supervised exercise class, walking programme or usual physiotherapy.

Stratification will be by hospital only and separate randomisation lists will be used for each hospital. Prior to randomisation each subject's group allocation preference will be sought and recorded by the Trial Co-ordinator in order to investigate whether treatment preference has any influence on outcomes.

The Trial Co-ordinator will telephone/text the Research Administrator who will provide a central, remote, telephone randomisation service, to obtain each consecutive subject's random group allocation. Following the baseline assessment an appointment for the relevant intervention will then be made by the Trial Co-ordinator. Each participant will receive a copy of 'The Back Book'[38] and be advised to read it before the first physiotherapy appointment. Participants allocated to the WP will be given an educational walking manual, and a Yamax Digiwalker Pedometer, instructed in its use and requested to wear it for seven days to record number of steps and habitual daily activity levels (frequency of walks, walk duration) in an exercise diary prior to the start of the intervention.

### Blinding

#### Clinicians

Due to the nature of the interventions it will not be possible to blind the participating clinicians to the group allocation of patients, but clinicians will not be involved in outcome assessment.

#### Patients

Due to the nature of the interventions it will not be possible to blind patients to their group allocation. The patient information leaflet will inform participants that they have an equal chance of receiving one of three physiotherapy approaches for low back pain management.

#### Assessors

A blinded researcher will administer all outcome measures for postal follow-up. The Trial Co-ordinator will not be involved in follow-up outcome assessment. The statistician will be unaware of group allocation until completion of data analyses.

### Sample Size

A total of 189 patients (n = 63 per group) will be required for 80% power to detect a 4 point difference between groups on the primary outcome, the Oswestry Disability Index [39], with 95% confidence using a two-tail between-within repeated measures ANOVA test of difference between group means. Based on the results of previous LBP trials investigating exercise [11] and using postal follow-ups [40], we anticipate a 30% loss to follow-up. Thus we aim to recruit 82 subjects per group (total 246 subjects).

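### The 30% attrition allowance is added (63 × 1.3 = 82) and not divided out (63 / 0.7 = 90), so at the planned loss 246 recruits give about 57 per arm and about 76% power, not 80%

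*Protocol article*

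**What the plan says.** The Sample Size section of the protocol article makes three linked statements.

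- Requirement: "A total of 189 patients (n = 63 per group) will be required for 80% power to detect a 4 point difference" on the ODI, the primary outcome.
- Test: "with 95% confidence using a two-tail between-within repeated measures ANOVA test of difference between group means".
- Attrition and the target derived from it: "we anticipate a 30% loss to follow-up. Thus we aim to recruit 82 subjects per group (total 246 subjects"). The 30% is drawn from earlier low back pain trials of exercise and of postal follow-up.

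The abstract repeats 246 as the recruitment figure. The primary objective, at the end of the Background, concerns change in disability at 6 months. Follow-up is at 3, 6 and 12 months. The section gives no SD and no within-subject correlation, and the article offers no other reason for 82.

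**The concern.** The three figures (63 needed, 30% lost, 82 recruited) cannot all hold. The target is presented as following from the other two, but it matches them only if the 30% is taken of the 63 who must remain. Loss to follow-up is a fraction of those who enter.

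What is at stake is the power claim for the primary outcome. If loss is what the plan expects, the trial ends below its own requirement, and a null result would be read against a stated 80% that the design does not provide. Because the abstract carries the same 246, the slip fixes the size of the trial.

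**Working it through.** **Inputs, all from Sample Size:** 63 per group (189 in total) for 80% power; two-sided 5%; difference of 4 ODI points; 30% loss; 82 per group (246 in total) recruited.

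**1. Reproduce the plan's target.** Adding the allowance:
- 63 × (1 + 0.30) = 81.9, rounded up to 82; 3 × 82 = 246. This matches exactly.

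**2. Divide the loss out.**
- 63 / (1 − 0.30) = 90 per group; 3 × 90 = 270.
- Difference from the plan: 8 per group, 24 in total. Rounding cannot explain it.

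**3. Numbers left at the planned loss.**
- 82 × 0.70 = 57.4 per group; 246 × 0.70 = 172.2 in total.
- Shortfall against the stated requirement: 189 − 172 = 17.

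**4. Largest loss that still leaves 63.**
- 1 − 63/82 = 0.232. That is 19 of 82 lost; 30% of 82 is 24.6.

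**5. Power at the retained number, taking the plan's premise that 63 gives 80%.** For a two-group comparison by normal approximation, the standardised difference at n = 63 is 1.960 + 0.842 = 2.802, and it scales with √n.
- n = 57.4: 2.802 × √(57.4/63) = 2.674; 2.674 − 1.960 = 0.714; power 76.2%.
- n = 57: 2.802 × √(57/63) = 2.665; 2.665 − 1.960 = 0.705; power 76.0%.

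The same calibration under other tests, for 57 to 57.4 per group:

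| Test assumed | Power |
|---|---|
| Pairwise, normal approximation | 76.0–76.2% |
| Pairwise t-test | 75.9–76.2% |
| Three-group F test | 75.6–75.9% |
| Bonferroni, 2 comparisons | 75.5–75.9% |
| Bonferroni, 3 comparisons | 75.3–75.6% |

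The drop hardly depends on the test, because the ratio 57.4/63 drives it.

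**6. What cannot be checked.** Under the two-group normal approximation, 63 per group implies an SD of 4 / (2.802 × √(2/63)) = 8.0. This is back-solved, not stated. It could stand for a raw score, a change score or an error term already reduced by the repeated measures. If the relevant SD were larger, 63 itself would be too few:

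| Assumed SD | n per group for 80% | Power at 63 | Power at 57.4 |
|---|---|---|---|
| 8 | 63 | 80% | 76% |
| 10 | 99 | 61% | 57% |
| 12 | 142 | 46% | 43% |
| 15 | 221 | 32% | 30% |

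The table shows only why the 76% is conditional. The article gives no basis for choosing a row.

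**The case against.** **Loss at 6 months may be below 30%.** The 30% is not tied to a visit. If it describes 12 months, the loss at 6 months, where the primary objective sits, could be smaller, and at 23% or less the 63 survive. This stands as a possibility and is why the shortfall is worded as conditional on 30% at the primary time point. The Sample Size section does not make this argument. It applies 30% without qualification.

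**Partial data could recover power.** An analysis that uses incomplete follow-up might do so, and the handling of missing data may lie in a plan not shown. However, the Data Analysis section names a repeated measures ANOVA, which conventionally uses complete cases, and the inflation for loss itself treats lost patients as not contributing.

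**The effect is small.** This stands. About 4 points of power are lost. No estimate is biased, and neither the type I error nor the question asked is affected. A reader might infer that the trial is seriously underpowered or has to be enlarged to 270; the figures do not support that.

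**Baseline adjustment might make up the gap.** A reader might infer that adjusting for baseline ODI would restore the lost power. The documents do not support this either. It needs a baseline-to-follow-up correlation and a definition of the SD behind the 63, and neither is given.

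**Conclusion.** The recruitment target is miscalculated. At the plan's own 30% loss, taken at the primary time point, 246 recruits leave about 57 per arm (172 in total) against a requirement of 63 (189), so the stated 80% power is not delivered. The retained numbers follow from the article's figures alone. The power of about 76% (75.3–76.2% across tests) also rests on the plan's unverified premise that 63 per arm gives 80%, and on lost patients contributing nothing to the primary comparison. This should be fixed, but it is a wrong power statement of modest size and not a flaw that undermines the design.

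**What to change.** Keep 246 and correct the statement in the Sample Size section, for example:

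> With 82 recruited per group (246 in total), a 30% loss at 6 months leaves about 57 per group. If 63 per group gives 80% power for a 4-point ODI difference, this gives about 76%. Power of 80% is kept only if loss is at most about 23%. At 30% loss, 90 per group (270 in total) would be needed.

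The cost is one sentence and a slightly less favourable stated power. No added recruitment and no change to the analysis are required.

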### Outcome Measures

At the baseline assessment sociodemographic data (i.e. age, gender, education level, social status, occupation and work status, past medical history, LBP history), cardiorespiratory fitness using the shuttle walk test [41], blood pressure, Body Mass Index (BMI, kg/m^2^) and any previous treatment will be documented by the Trial Coordinator. A combination of recommended self-report valid and reliable outcome questionnaires [42] detailed below, and objective measurement will be used at baseline and follow-up (3, 6 and 12 months). The satisfaction questionnaire will only be administered at the end of scheduled intervention period (3 months).

### Clinical Outcomes

The **primary outcome measure **will be a change in:

(i) *Functional disability *due to LBP measured by the Oswestry Disability Index (ODI) [43]

The **secondary outcome measures **will be changes in:

(ii) *Pain *using Numerical Rating Scales for current and worst pain [44]

(iii) *Health-related quality of life *measured by the EuroQol questionnaire [45]

(iv) *Psycho-social beliefs *using the Fear Avoidance Beliefs Questionnaire [46] and the Back Beliefs Questionnaire [47]

(v) *Employment status and number of days reported sick leave over the past year *for those in paid employment only

(vi) *Self-report physical activity levels *using the International Physical Activity Questionnaire (IPAQ) [48],

(vii) *Objective physical activity levels *using an activPal™ device: a valid and reliable measure of walking that is capable of recording steps, time spent lying/sitting, standing and stepping under free living conditions [49] previously used by some of the authors in another LBP trial [50]. A sample of convenience of participants from each group will be requested to wear the activPAL™ on 3 separate occasions each lasting 7 days (1) at baseline, (2) 3 months and (3) 6 months after initial randomisation.

(viii) Self efficacy questionnaire [51]

(ix) Readiness to change questionnaire [52]

(x) *Patient satisfaction *will be assessed using Likert scales assessing satisfaction with outcome and satisfaction with care at 3 months [53]

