### Hypotheses Tested

The trial will test two 'null' hypotheses. The primary null hypotheses is that,

(a). in people referred for physiotherapy for chronic LBP there is no difference in clinical outcome and costs between those receiving a walking programme, a supervised general exercise programme and usual physiotherapy;

The secondary null hypothesis is that:

(b). subjects that have received a walking programme or supervised general exercise programme will not have changed daily physical activity levels compared to those who have received usual physiotherapy

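### Objective physical activity (activPAL) is compared between arms in a convenience sample, so randomisation does not protect that one comparison; IPAQ still gives hypothesis (b) a randomised test

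*Protocol article*

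**What the plan says.** All references are to the protocol article.

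- **Hypotheses Tested, (b).** The secondary null hypothesis is that patients in the walking programme or the exercise class "will not have changed daily physical activity levels compared to those who have received usual physiotherapy".
- **Clinical Outcomes, (vi).** Self-reported activity is measured "using the International Physical Activity Questionnaire (IPAQ) [48"], with no restriction to a subsample.
- **Clinical Outcomes, (vii).** Objective activity is measured by activPAL: "A sample of convenience of participants from each group will be requested to wear the" device for seven days on each of three occasions, "1) at baseline, (2) 3 months and (3) 6 months after initial randomisation".
- **Data Analysis.** Analysis is by intention to treat, and each outcome is tested between groups for its difference from baseline. No exception is made for activPAL.
- **Blinding, Patients.** "it will not be possible to blind patients to their group allocation".
- **Randomisation.** The Trial Co-ordinator contacts the Research Administrator "to obtain each consecutive subject's random group allocation". Walking-arm patients then receive a pedometer and are "requested to wear it for seven days to record number of steps and habitual daily activity levels" before treatment starts.
- **Outcome Measures.** A general sentence says that questionnaires and "objective measurement will be used at baseline and follow-up (3, 6 and 12 months").

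**The concern.** A between-arm comparison is protected by randomisation when the people measured are those randomised, or a subset chosen without regard to arm. A convenience sample drawn from each group meets neither condition. Patients know their arm and the Trial Co-ordinator knows it too, so approach and consent can both depend on it. A week of step recording may, for example, appeal more to an engaged walking-programme patient than to someone receiving usual physiotherapy.

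At stake is the interpretation of the one activity outcome that does not rely on self-report by unblinded patients. As written, a between-arm difference in a self-selected subset would be tested and reported in the same way as the randomised outcomes, and it could create or hide an activity effect. The choice of a convenience sample is stated in the protocol, so it is not a detail left to an analysis plan.

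**Working it through.** **1. Does any stated safeguard cover the activPAL subsample?** Controlling bias relies on randomisation, concealed allocation, blind assessment and intention to treat. None of these governs who is picked to wear the device. The protocol does use random 20% samples elsewhere, for treatment records (Protocol protection) and cost diaries (Cost Outcomes). It uses convenience selection where the subsample carries an outcome comparison.

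**2. When are wearers chosen?** This is not stated. Choosing from each group reads most naturally as choosing after groups exist. If they were chosen before allocation, mainly generalisability would suffer.

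**3. What bias follows?** Let D be change from baseline, S being a wearer, and 1 and 0 two arms. Then

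bias = {E[D | S, arm 1] − E[D | arm 1]} − {E[D | S, arm 0] − E[D | arm 0]}.

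- If willing patients are simply more active throughout, by the same amount c at baseline and follow-up, the shift in change is c − c = 0.
- If willingness correlates with D at r1 in one arm and r0 in the other, and the most willing fraction p wears the device, bias = (r1 − r0) × m(p) SDs of change. Here m(p) is the mean of the top fraction p of a standard normal: m(0.5) = 0.399/0.5 = 0.798 and m(0.25) = 0.318/0.25 = 1.27.

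**4. Illustration.** The document gives neither p nor any correlation, so every input except the 82 per arm is assumed. The simulation had no true effect, a two-sample t-test at 5% and 6,000 replicates.

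| Fraction wearing | r1, r0 | (r1 − r0) × m(p) | Simulated shift (SD) | Simulated type I error |
|---|---|---|---|---|
| half | 0.3, 0.3 | 0 | 0.00 | 5.4% |
| half | 0.3, 0 | 0.3 × 0.798 = 0.24 | 0.24 | 19.8% |
| half | 0.5, 0 | 0.5 × 0.798 = 0.40 | 0.40 | 45.8% |
| quarter | 0.3, 0.3 | 0 | 0.00 | 5.2% |
| quarter | 0.3, 0 | 0.3 × 1.27 = 0.38 | 0.38 | 22.3% |
| quarter | 0.5, 0 | 0.5 × 1.27 = 0.64 | 0.63 | 53.9% |
| all | 0.5, 0 | 0 | 0.00 | 4.7% |

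Bias needs selection that differs by arm and relates to change. Identical selection, or measuring everyone, keeps the error near 5%. The rows with r0 = 0 are a sharp contrast: strong selection in one arm and none in the other.

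**5. The baseline week.** The walking arm wears a pedometer for seven days before treatment, and every arm starts within one week of randomisation (Interventions). A seven-day activPAL baseline begun after allocation would therefore largely coincide with the pedometer week in that arm, or run into treatment. The Background section itself describes pedometers as motivating more activity. Whether the activPAL baseline does begin after allocation is not stated.

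**6. Time points.** The Outcome Measures sentence is general and runs to 12 months. The activPAL item is specific and stops at 6 months.

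**The case against.** The strongest reply is that the text does not establish several things a reader might infer.

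- **That wearers are certainly chosen after allocation, by the Trial Co-ordinator.** The article says neither when nor by whom. Naming each group could mean only that all three arms are represented. This stands; later selection is the natural reading, not a stated fact.
- **That hypothesis (b) has no randomised test.** It does. IPAQ measures the same construct with no stated subsample restriction. This stands, with the limit that IPAQ is self-report from unblinded patients. The article does not rank the two measures.
- **That the bias is about 0.24 SD, roughly half the effect the trial was sized for.** Neither part is supported. The outcome is change from baseline, so a correlation between willingness and activity level alone can cancel. The 0.5 SD yardstick belongs to disability: 63 per group for 4 ODI points implies SD = 4 × √(63/2) / (1.960 + 0.842) = 8.01, and 4/8.01 = 0.50. It says nothing about activity.
- **That the pedometer contaminates the activPAL baseline.** Overlap is plausible from the timetable, but it depends on when that baseline week begins.
- **That the 6- and 12-month statements conflict in substance.** One is a general sentence pointing to the details below it and the other is the specific schedule, so this is a wording matter.
- **That the missing subsample size is a fault.** An article may leave it to the full protocol.

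Random flagging is also not a complete cure. Non-wear at 3 and 6 months can still differ by arm. The core of the point survives all of this: the article fixes convenience selection and then tests the result as it tests the randomised outcomes.

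**Conclusion.** The concern holds in a limited form. The activPAL between-arm comparison, as designed, is not protected by randomisation, because a non-random subset of unblinded patients is tested between groups under an intention-to-treat heading. Bias is a risk, not a certainty. Its size in change from baseline cannot be derived from the document; the illustrative figures run from nil to about 0.6 SD, depending wholly on assumed selection that differs by arm.

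The effect is confined to one secondary outcome. The primary outcome is untouched, and IPAQ keeps a randomised, self-reported test of hypothesis (b). The conclusion rests on the natural reading that wearers are chosen once groups exist. If they are chosen before allocation, the article should say so, and the concern reduces mainly to generalisability. It is worth correcting, but it does not undermine the trial.

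**What to change.** 1. Have the trial statistician flag the planned number of activPAL wearers at random on each hospital's centrally prepared list. Invite the flagged patients before their allocation is disclosed, and analyse them in the arm to which they were randomised.
2. Where feasible, start the activPAL baseline week before the walking arm's pedometer is issued.
3. If steps 1 and 2 cannot be done, label the activPAL between-arm comparison exploratory and rest hypothesis (b) on IPAQ.
4. Reconcile the wording on the last objective time point between Outcome Measures and Clinical Outcomes (vii).

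**Cost.** The number of devices does not change, and the hospital lists already exist. Step 1 takes away some scheduling freedom. Step 2 is less clearly cheap: holding back disclosure for a seven-day wear delays flagged patients and may need a further contact, which is why it is conditional. Steps 3 and 4 need only text changes.
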